## Materials and methods

Study design

This is a single-center, double-blind, placebo-controlled, parallel arms, superiority randomized clinical trial. The maximum duration of the intervention will be 28 days while the duration of follow-up will be till hospital discharge. The study will be conducted in the ICU of the largest government hospital in the central region of Saudi Arabia. The ICU has 110 beds, fully equipped with invasive and non-invasive monitoring and ventilation capabilities. It is covered round the clock by intensivists, with a nurse-patient ratio of 1: 1.

Inclusion and Exclusion Criteria

Inclusion criteria: Adults (≥18 years), ICU admission, mechanical ventilation for <7 days, and ARDS diagnosed within 24 hours per the Berlin Definition [1], which includes: a) Chest x-ray showing bilateral opacities, not fully explained by effusions, lobar/lung collapse, or nodules; b) Respiratory failure not fully explained by cardiac failure or fluid overload, and exclusion of hydrostatic edema (by echocardiography); c) Oxygenation and ventilator settings matching one of the three categories of ARDS: Mild: 200 mmHg < PaO2/FIO2 ≤ 300 mmHg with positive end-expiratory pressure (PEEP) or continuous positive airway pressure (CPAP) ≥ 5 cm H2O. Moderate: 100 mm Hg < PaO2/FIO2 ≤ 200 mm Hg with PEEP ≥ 5 cm H2O. Severe: PaO2/FIO2 ≤ 100 mm Hg with PEEP ≥ 5 cm H2O.

Exclusion criteria: Pregnant or lactating ladies; Patients who are not expected to survive more than 48 hours, according to the treating team; Mechanical ventilation is expected to continue for less than 48 hours (due to rapid recovery) according to the treating team; Advanced directive of Do Not Resuscitate (DNR); Refusal to participate in the trial by the patient or official surrogate; Known allergy to furosemide; Previous enrollment in the trial (a patient can only be enrolled once).

Study objectives

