The primary objective is 28-day mortality in the ICU, starting from the day of randomization. Secondary objectives include: All-cause hospital mortality, ICU and hospital length of stay (LOS), the difference in P/F ratio between day one and day seven (not to be calculated for patients who are censored before seven days), 28 days ventilator-free days (VFD) (defined as days without mechanical ventilation till day 28 starting from day of enrollment, as long as the patient is alive); patients still mechanically ventilated at day 28, or died by day 28, will be assigned zero VFD. If the artificial airway is shifted from endotracheal tube to tracheostomy, they will still be considered mechanically ventilated until they are liberated from mechanical ventilation and are spontaneously breathing. With respect to a successful extubation rate, defined as extubated and not requiring re-intubation for 72 hours, tracheostomy is not considered successful extubation. Examples of adverse events will be hypersensitivity reactions - of any magnitude, abnormal lab investigations, specifically electrolytes and renal function tests, and volume of urine output.

Enrollment, randomization, and allocation concealment

After obtaining the informed consent of a legal guardian, randomization will be obtained via a phone call providing a study code, without breaking the concealment of allocation. Randomization will be performed using variable block sizes (4, 6, or 8), stratified by ARDS severity (mild, moderate, severe).

Blinding

Furosemide and saline are identical in appearance, color, and solution characteristics. The investigational medication will be prepared by an independent pharmacist in identical vials, labeled only with study code and patient identifiers, and delivered to the clinical area. The flow of patients' enrollment is depicted in Figure 1.

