Assuming a mortality rate of 40% in the control group [2,8], and aiming to detect an effect size of 10% absolute reduction in mortality in the intervention group with a power of 80% and type I error rate of 5%, we estimated the sample size to be 712 patients (356 in each group), with 10% inflation to compensate for possible loss of follow-up (patients transferred to other healthcare facilities), we plan to recruit a total of 784 patients, allocated in a 1: 1 ratio as 392 patients in each group.

Statistical plan

Intention-to-treat (ITT)-based analysis: Data of the patients will be analyzed in the group to which they were randomized, regardless of the actual intervention they received. Continuous variables will be summarized as mean ± standard deviation (SD) or median and interquartile range (IQR) depending on the normality assumption, tested for by the Shapiro-Wilk normality test. Discrete variables will be summarized as frequency (count) and percentage. Time-to-event data will be 28-day mortality as the event and duration since randomization as the time variable, with right censoring.

For the primary outcome, comparison between both groups for 28-day mortality will take place by the chi-square test of association, for secondary outcomes, groups will be compared by the chi-square test of association or Fisher’s exact test, according to data count in each cell of the two by two contingency table, while continuous variables will be compared between groups by the student's t-test or the non-parametric Wilcoxon Rank-Sum test.

We will perform a survival analysis using the time-to-event data, in the form of a Kaplan-Meier Survival curve as compared by the log-rank test.

As a sensitivity test for the primary outcome, we will fit two regression models. First will be a multinomial logistic regression model, using backward elimination to retain only variables with p-value < 0.1 and the severity of ARDS as the multinomial levels in the model. A multivariable proportional hazard model (Cox regression) will be carried out in a similar way, utilizing days from randomization to event as the time variable. Additionally, we will present a per-protocol analysis of the primary outcome.

A priori subgroup analyses will examine the primary outcome with regard to sex, the median age of the cohort, ARDS severity, and adjunct and rescue therapies used (such as corticosteroids, prone positioning, and ECMO).

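### Successful extubation has no survival condition, so a death within 72 hours of extubation can count as a success (minor)

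*Protocol article*

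**What the plan says.** In the protocol article, under Materials and methods, Study objectives, successful extubation is a secondary outcome "defined as extubated and not requiring re-intubation for 72 hours". One exception follows: "tracheostomy is not considered successful extubation". Death is not mentioned. Table 2 in the Results section lists the outcome by name only.

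The same paragraph does state a death rule for ventilator-free days (VFD): "patients still mechanically ventilated at day 28, or died by day 28, will be assigned zero VFD".

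Under Statistical plan, for binary secondary outcomes "groups will be compared by the chi-square test of association or Fisher’s exact test". The general analysis rule is intention to treat: "Data of the patients will be analyzed in the group to which they were randomized". No separate handling of death is given for the extubation outcome, and nothing restricts its denominator to extubated patients.

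**The concern.** The definition sets two conditions, extubation and no requirement for re-intubation over 72 hours, and one exclusion. A patient who dies in that window without having required re-intubation meets both conditions and is not caught by the exclusion. Such a death then enters the two-by-two table as a success.

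A related group is unclear rather than wrong. A do-not-resuscitate directive excludes patients only at entry, and the protocol does not address limits of care set later. A patient who deteriorates after extubation and is not offered re-intubation could be scored either way, depending on whether the assessor records need or receipt.

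At stake are the reported success rate in each arm, which can be too high, and the difference between arms, which is distorted if such deaths are not equally frequent in both.

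**Working it through.** **1. What the literal rule does.** Take a patient extubated at time *t*.

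| Course after extubation | Result under the stated definition |
|---|---|
| Alive at *t* + 72 h, re-intubation not required | Success |
| Re-intubated before *t* + 72 h, alive or dead afterwards | Not a success |
| Dies before *t* + 72 h, re-intubation not required | Success, read literally |
| Dies before *t* + 72 h, re-intubation needed but not offered | Ambiguous |

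The third row is the defect and the fourth the ambiguity.

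**2. The plan's own figures.** No rate or power is stated for this outcome, so there is no stated figure to reproduce for it. The arm size used below comes from the Sample size calculation: "Assuming a mortality rate of 40% in the control group", "aiming to detect an effect size of 10% absolute reduction in mortality", 80% power and two-sided 5%. The pooled-variance formula is

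n = [1.960 × √(2 × 0.35 × 0.65) + 0.842 × √(0.40 × 0.60 + 0.30 × 0.70)]² / 0.10² = 356 per arm, or 712 in total.

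Multiplying by 1.10 gives 391.6, rounded up to 392 per arm (784). These agree with the protocol and do not depend on the extubation outcome.

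**3. Patients affected per arm.** Let *e* be the share of an arm extubated, and *q* the share of those who die within 72 hours without re-intubation. The document gives neither, so both are assumptions. Patients affected = 392 × *e* × *q*; percentage points of the arm = 100 × *e* × *q*.

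| *e* | *q* = 1% | *q* = 3% | *q* = 5% | *q* = 10% |
|---|---|---|---|---|
| 50% | 2.0 (0.5 pt) | 5.9 (1.5) | 9.8 (2.5) | 19.6 (5.0) |
| 60% | 2.4 (0.6) | 7.1 (1.8) | 11.8 (3.0) | 23.5 (6.0) |
| 70% | 2.7 (0.7) | 8.2 (2.1) | 13.7 (3.5) | 27.4 (7.0) |

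The range is 0.5 to 7 points of an arm. It is an upper reading: it counts every such death as a success, including those in the ambiguous row.

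**4. Effect on the comparison.** Assume 60% extubated and 12% of those re-intubated in both arms. As written, success is 0.60 × (1 − 0.12) = 52.8% in each arm, a difference of 0.

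- Deaths in the window 5% (control) and 2% (furosemide): requiring survival gives 0.60 × (1 − 0.12 − 0.05) = 49.8% and 0.60 × (1 − 0.12 − 0.02) = 51.6%, a difference of +1.8 points.
- Rates reversed: −1.8 points.
- Rates equal at 2% or at 5%: a difference of 0, with both arms overstated by 1.2 or 3.0 points.

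The sign of the distortion therefore follows the window deaths in each arm, which the document does not let us predict.

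**5. Scale.** With 392 per arm and success near 60% (an assumption), the standard error of the difference is √(2 × 0.6 × 0.4 / 392) = 3.5 points. A shift of 1.8 points is about half a standard error.

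**The case against.** The strongest reply is that the criterion speaks of *requiring* re-intubation, not of receiving it. A patient who fails after extubation and is left without a tube because care was limited arguably did require one, and so already fails. This stands in part. It is why that group is called ambiguous here, and why the clear defect is confined to deaths with no such requirement.

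Second, the 72 hours may be read as a period that must be completed, which a patient who dies at 10 hours has not done. That is a fair reading of intent, but the text does not say it. Nor is this simply a detail left to a fuller document, because the article fixes the definition itself, with a window and an exception.

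Third, a reader might infer from the VFD rule that the protocol contradicts itself. It does not. VFD penalises any death by day 28, whereas extubation success looks at 72 hours. A patient extubated on day 5 who dies on day 20 scores zero VFD and is still a success under the repaired definition. The contrast shows only that a death rule was written for the neighbouring outcome and not for this one.

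Fourth, a reader might infer that the rule systematically favours the arm with more deaths, so that a life-saving drug looks worse. That needs the same fraction *f* of all deaths to fall in the window in both arms. At 40% v 30% mortality the difference would then shrink by 0.10 × *f*, or 0.5 to 2 points for *f* of 5-20%. Neither that range nor an equal fraction has any basis in the document, and if the fractions differ the bias can go either way.

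Finally, this is one secondary outcome, tested without multiplicity correction, and the protocol itself warns that such results are not conclusive. ICU and hospital mortality appear in the same table, so an excess of deaths would be visible. That limits the severity but does not remove the point.

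**Conclusion.** The point holds as a minor defect of definition. Taken literally, the rule scores a death within 72 hours of extubation, without re-intubation having been required, as a success, and it leaves unclear how to score a patient who needed re-intubation but was not offered it. The size rests wholly on assumed rates and is illustrative. The document supports no direction of bias between the arms. The primary outcome, the sample size of 712 (784 after inflation) and the interim stopping rules are unaffected.

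**What to change.** Define the outcome as: *extubated, and alive without re-intubation at 72 hours*. State that death within 72 hours of extubation is not a success, and that all randomised patients stay in the denominator, which agrees with the existing intention-to-treat rule. Keep the tracheostomy exception. This replaces a judgement of need with observed status, so a patient who dies in the window is a failure whether or not re-intubation was offered.

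The cost is a few words, settled before unblinding. The 72-hour window already needs extubation and re-intubation times, and the survival analysis already needs time to death. If death is recorded only by date, a clock time should be added. No change to sample size or analysis method follows.

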**Figure 1 FIG1:**
[figure not shown]
Flowchart of patients' enrollment ITT = Intention to Treat, PP = Per Protocol

Study intervention

The study intervention should begin within six hours of randomization. Identical vials of 4 ml containing either furosemide (intervention) or 0.9% saline (placebo). In this study, we will follow a nebulized furosemide protocol similar to that reported in a study on nebulized furosemide in COVID-19 patients [12].

The intervention medication is 40 mg furosemide in 4 ml of 0.9% saline, administered every six hours via the ventilator circuit over 30 minutes. The nebulization circuit used in our ICU is Aerogen® (Galway, Ireland). The intervention continues till extubation, death, or completion of 28 days, whichever comes first. The intervention will continue if the artificial airway is shifted from the endotracheal tube to tracheostomy but not for re-intubated patients.

The control group receives a similar color and volume of 0.9% saline following the same intervals, route, and duration.

Common management

This is a pragmatic trial; the study protocol does not control every aspect of the management, apart from the intervention medication, trying to resemble real-life scenarios of management, where different treating teams may have slightly different methods of management, which may provide higher external validity [27].

However, our center follows evidence-based guidelines and protocols for the management of ARDS [28], and treating teams will be encouraged to follow those guidelines such as protective lung strategy. Adjuvant and rescue therapies will be allowed, such as (but not limited to) prone positioning and extracorporeal membrane oxygenation (ECMO), and the use of other medications such as glucocorticoids, antibiotics, and neuromuscular blocking agents.

Similarly, our center adopts practices of early enteral feeding, light sedation, and daily sedation vacation when applicable, deep vein thrombosis (DVT) and gastrointestinal (GIT) prophylaxis, and early weaning and extubation using a standardized protocol. Antibiotics are prescribed after consulting infectious disease specialists.

Sample size calculation

Assuming a mortality rate of 40% in the control group [2,8], and aiming to detect an effect size of 10% absolute reduction in mortality in the intervention group with a power of 80% and type I error rate of 5%, we estimated the sample size to be 712 patients (356 in each group), with 10% inflation to compensate for possible loss of follow-up (patients transferred to other healthcare facilities), we plan to recruit a total of 784 patients, allocated in a 1: 1 ratio as 392 patients in each group.

Statistical plan

Intention-to-treat (ITT)-based analysis: Data of the patients will be analyzed in the group to which they were randomized, regardless of the actual intervention they received. Continuous variables will be summarized as mean ± standard deviation (SD) or median and interquartile range (IQR) depending on the normality assumption, tested for by the Shapiro-Wilk normality test. Discrete variables will be summarized as frequency (count) and percentage. Time-to-event data will be 28-day mortality as the event and duration since randomization as the time variable, with right censoring.

For the primary outcome, comparison between both groups for 28-day mortality will take place by the chi-square test of association, for secondary outcomes, groups will be compared by the chi-square test of association or Fisher’s exact test, according to data count in each cell of the two by two contingency table, while continuous variables will be compared between groups by the student's t-test or the non-parametric Wilcoxon Rank-Sum test.

We will perform a survival analysis using the time-to-event data, in the form of a Kaplan-Meier Survival curve as compared by the log-rank test.

As a sensitivity test for the primary outcome, we will fit two regression models. First will be a multinomial logistic regression model, using backward elimination to retain only variables with p-value < 0.1 and the severity of ARDS as the multinomial levels in the model. A multivariable proportional hazard model (Cox regression) will be carried out in a similar way, utilizing days from randomization to event as the time variable. Additionally, we will present a per-protocol analysis of the primary outcome.

A priori subgroup analyses will examine the primary outcome with regard to sex, the median age of the cohort, ARDS severity, and adjunct and rescue therapies used (such as corticosteroids, prone positioning, and ECMO).

There will be no correction for multiple testing; accordingly, results of secondary outcomes and sub-group analyses should not be considered conclusive and must be cautiously interpreted.

All statistical tests are two-sided and considered statistically significant if the p-value is <0.05.

Interim analysis and stopping rules

We will perform one interim analysis when 50% of the sample size is recruited, to assess the efficacy of the intervention, with the possible early stopping of the trial based on O’Brien-Fleming alpha spending functions [29]. The stopping rules are: 1- Stopping for superiority: If the interim analysis results in a critical z-score of +2.963 or more, yielding a p-value of 0.0031 or less; 2- Stopping for harm: If the interim analysis results in a critical z-score of -2.963 or less, yielding a p-value of 0.0031 or less; 3- Stopping for futility: If the interim analysis results in a critical z-score between +0.595 and -0.595, corresponding to a p-value of 0.55 (Figure 2).

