## Discussion

This may be the first RCT to explore the effect of nebulized furosemide on the outcomes of critically ill, mechanically ventilated ARDS patients, a hypothesis that stems from furosemide’s anti-inflammatory effects, its availability, direct delivery to the lung tissue, in addition to its wide safety margin, and is supported by the trend of mortality benefit in COVID-19 patients previously reported [12].

Indeed, ARDS is a condition characterized by both high volume and impact. With regards to volume, ARDS involves 10% of all ICU patients and 23% of mechanically ventilated patients, which translates into an incidence of 5.5 cases per ICU bed per year [8]. As for the impact, ARDS was associated with about 35%, 40%, and 45% mortality for mild, moderate, and severe ARDS, respectively, as defined by the P/F ratio [30]. Hence, an intervention with the potential to lower mortality, of any magnitude, is worth exploring.

At the completion of this study, findings will be analyzed to confirm or refute the hypothesis. Our interpretation, conclusion, and recommendations will be presented, accompanied by an objective and transparent discussion of the work’s limitations.

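### Randomisation is stratified by ARDS severity, but the primary chi-square and the log-rank test use neither the stratum nor any collected baseline; this costs efficiency, not validity

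*Protocol article*

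**What the plan says.** All references are to the protocol article.

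- **Enrollment, randomization, and allocation concealment:** allocation is "stratified by ARDS severity (mild, moderate, severe").
- **Statistical plan, primary outcome:** "comparison between both groups for 28-day mortality will take place by the chi-square test of association".
- **Statistical plan, survival analysis:** the time-to-event data are shown "in the form of a Kaplan-Meier Survival curve as compared by the log-rank test". No stratification is mentioned for either test.
- **Statistical plan, sensitivity analyses:** a multinomial logistic model is fitted, "using backward elimination to retain only variables with p-value < 0.1 and the severity of ARDS as the multinomial levels in the model". A Cox model is to be built in the same manner. ARDS severity is also a planned subgroup.
- **Sample size calculation:** "Assuming a mortality rate of 40% in the control group", a 10-point absolute reduction, 80% power and 5% type I error give 712 patients (356 per arm), inflated to 784 (392 per arm).
- **Discussion:** "about 35%, 40%, and 45% mortality for mild, moderate, and severe ARDS".
- **Results, dummy Table 1:** age and SOFA at randomisation are among the baseline variables to be collected. The same section promises differences with 95% confidence intervals.

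**The concern.** When allocation is balanced within strata that predict the outcome, part of the variation between patients can no longer contribute to chance differences between the arms. An unstratified test still counts that variation in its standard error, so it is slightly too cautious for the design that produced the data. The article's own figures make severity prognostic, so this applies here.

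The same reasoning extends to baseline variables that predict death but were not used to stratify. Leaving them out is not inconsistent with the design, but it gives up precision that the data already collected could provide.

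The planned sensitivity models do not fill the gap:

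- A multinomial model with severity as its levels does not clearly estimate a treatment effect on death adjusted for severity.
- Backward elimination at p<0.1 guarantees no covariate a place, not even the stratification factor. As written, the Cox model inherits this.
- A subgroup analysis gives results within each stratum, not one adjusted overall effect.

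At stake is some power for the primary comparison and the lack of a prespecified adjusted estimate.

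**Working it through.** **1. Reproduce the plan's sample size.** Inputs from the sample size section: 40% versus 30% (mean 35%), with two-sided 5% and 80% power.

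n per arm = [1.960·√(2·0.35·0.65) + 0.8416·√(0.40·0.60 + 0.30·0.70)]² / 0.10²
= [1.960·0.6745 + 0.8416·0.6708]² / 0.01 = 355.9, rounded up to **356 per arm, 712 in total**.

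This matches the plan exactly, for an unadjusted comparison without continuity correction. Power is 80.0% at 356 per arm and 83.7% at 392 per arm.

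**2. Share of outcome variance explained by severity.** The stratum mortality of 35/40/45% comes from the Discussion. The article gives no severity mix, so the mix is assumed.

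R² = Σ w(p − p̄)² / [p̄(1 − p̄)]

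For an assumed mix of 30/45/25: p̄ = 0.3975, numerator 0.00137, denominator 0.2395, so R² = 0.0057 (0.57%).

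Other assumed mixes, with the effect taken as null, as a constant 10-point reduction or as a constant risk ratio of 0.75:

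| Assumed mix (mild/moderate/severe) | Variance explained |
|---|---|
| 30/47/23 | 0.44-0.58% |
| 20/50/30 | 0.41-0.53% |
| equal thirds | 0.56-0.73% |
| 50/0/50 (extreme) | 0.84-1.10% |

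**3. Convert to power.** Adjustment scales the variance by about (1 − R²):

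Power = Φ{[0.10 − 1.96·SE₀·√(1−R²)] / [SE₁·√(1−R²)]}, with SE₀ = √(2·0.35·0.65/356) = 0.03575 and SE₁ = √(0.45/356) = 0.03555.

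| R² | Power at 356 per arm | Total N for 80% power |
|---|---|---|
| 0 | 80.0% | 712 |
| 0.3% | 80.1% | 710 |
| 0.7% | 80.3% | 708 |
| 1.0% | 80.4% | 706 |
| 5% (assumed) | 82.0% | 678 |
| 10% (assumed) | 84.0% | 642 |
| 15% (assumed) | 86.0% | 606 |

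Severity alone falls in the rows up to about 1%. The last three rows add age and SOFA. Their strength is not in the article, so 5-15% is an assumption. Put the other way, 712/(1 − R²) is 749 at 5% and 838 at 15%, the same as having about 5% to 18% more patients.

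**4. Check by simulation.** 20,000 replicates, N = 712, stratified blocks of 4, 6 or 8, mix 30/47/23.

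| Stratum mortality | Quantity | Plain chi-square | Stratified Mantel-Haenszel |
|---|---|---|---|
| 35/40/45% | Type I error | 4.9% | 4.9% |
| 35/40/45% | Power, 10-point reduction | 80.0% | 80.1% |
| 25/40/55% (assumed, wider) | Type I error | 4.5% | 5.1% |
| 25/40/55% (assumed, wider) | Power, 10-point reduction | 81.2% | 82.7% |

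The plain test does not inflate type I error. It becomes visibly conservative only if the strata differ more than the article says.

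**The case against.** The strongest reply is that the defect is negligible on the article's own figures. At R² = 0.57% the standard error is too large by a factor of 1/√(1 − 0.0057) = 1.003. On a 95% CI half-width of 1.96·0.0356, about 7.0 points, that is about 0.02 points. This stands: the stratum alone is an argument for coherence, not for power.

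Second, the larger gain rests on an assumed R² for age and SOFA, which are not stratification factors. This also stands. The gain must be stated as conditional, and adjustment beyond the stratifier is a recommendation, not the correction of an error.

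Third, the plan includes adjusted models and a severity subgroup, so severity is not ignored throughout. That is true, but for the reasons given above none of these yields a prespecified adjusted effect. The log-rank is not the primary test, and an analysis plan not shown might stratify it. The primary test, however, is fixed in the article as a chi-square.

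Three stronger readings are tempting but not supported:

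- **That the primary test is invalid or inflates type I error.** The simulation shows 4.9%, or lower if the strata differ more.
- **That power is already below 80%.** The 712 reproduces at 80.0%, and 392 evaluable per arm would give 83.7%. The interim futility rule could cost some power: if always followed, with a final critical value of 1.96, power would be about 78% at 356 per arm and about 82% at 392. But the Figure 2 caption says only that the trial may stop, and the result depends on actual losses. A shortfall is not established and is a separate matter.
- **That severity was chosen as a stratifier because it predicts death.** The randomisation section gives no reason. The 35/40/45% figures appear in the Discussion to describe the burden of ARDS.

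**Conclusion.** The concern holds as a point of efficiency and design coherence. The primary chi-square and the log-rank do not use the randomisation stratum or any baseline variable, and the sensitivity models do not supply a prespecified adjusted effect. The chi-square remains valid, and the sample size is correct for it.

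Stratifying by severity alone is worth about 0.1 to 0.4 points of power, or about 2 to 6 of 712 patients. Adding age and SOFA is worth about 2 to 6 points (80% to 82-86%).

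These sizes assume that the quoted mortality by severity carries over to 28-day ICU mortality, that the severity mix lies within the range shown, that variance falls in proportion to 1 − R², and, for the larger gain, that R² is 5-15%. The change is worth making because it is nearly free, not because the present test is wrong.

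**What to change.** Before any unblinded look at outcomes, including the interim analysis, amend the statistical plan as follows:

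1. **Primary analysis:** a logistic model for 28-day ICU mortality with treatment, ARDS severity as randomised, age and SOFA at randomisation. All terms are fixed in advance, with no variable selection. Report a standardised risk difference with 95% CI, which keeps the absolute scale of the sample size and of the planned outcome table. At minimum, use a Cochran-Mantel-Haenszel test stratified by severity, with the Mantel-Haenszel risk difference and 95% CI.
2. **Interim:** take the interim z-score from the same analysis as the final test.
3. **Survival:** stratify the log-rank test by severity.
4. **Supportive:** keep the plain chi-square as a supportive result.

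The cost is wording only. Every variable is already collected, and the sample size need not change.
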